### Intervention

The intervention is provided in addition to usual care. In this study the same intervention will be delivered by two different modes, via telephone or via mHealth (described in sections below) (Fig. 1). The intervention period will be 18 weeks, commencing as early as possible from the time of diagnosis. Following an initial assessment, weekly or fortnightly reviews will continue throughout the intervention period, as agreed by the dietitian and the participant. Participants who are in hospital at the time of a planned dietetic phone review will not receive their intervention that week, as it is assumed that whilst in hospital they will be receiving dietetic input as required, as part of ‘usual care.’ The intervention will re-commence once the participant has been discharged home, and the intervention timeline will not be suspended.

The intervention will be delivered by a research dietitian with experience in provision of clinical care to this population. The intervention will be delivered according to a Standard Operating Procedure that specifies a list of behaviour change techniques that can be employed through both of the intervention arms (Table 1). The behaviour change techniques specified are drawn from the Behaviour Change Technique Taxonomy (v1) [24]. The dietitian will set goals and instructions on how to perform the behaviour with the participant and provide tailored nutritional recommendations based on the participant’s history and nutrition impact symptoms. In the subsequent review session reviewing of goals will feature and other secondary behaviour techniques can be used if the initial behaviour techniques are not successful (Table 1).

**Table 1 Tab1:** Example of behaviour change techniques [24] used at the initial assessment (t_1_) and subsequent reviews (t_2_-t_18_)

	Behaviour change technique	Definition [24]	Example	Classification^a^
Initial assessment (t_1_)	Goal setting (behaviour)	Set or agree on a goal defined in terms of the behaviour to be achieved	Set the goal of eating 5 pieces of fruit per day	Routinely Used
	Goal setting (outcome)	Set or agree on a goal defined in terms of a positive outcome of wanted behaviour	Set a weight gain goal (e.g. 0.5 kg over one week) as an outcome of changed eating patterns	Supplementary

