	Problem solving	Analyse, or prompt the person to analyse, factors influencing the behaviour and generate or select strategies that include overcoming barriers and/or increasing facilitators	Prompt the patient to identify potential barriers to them drinking a particular supplement (e.g. bad taste) and discuss ways in which they could overcome them (e.g. mix with strawberries)	Supplementary
	Action planning	Prompt detailed planning of performance of the behaviour (must include at least one of context, frequency, duration and intensity). Context may be environmental (physical or social) or internal (physical, emotional or cognitive)	Prompt planning the drinking of a supplement at a particular time (e.g. before work) on certain days of the week	Routinely Used
	Monitoring of behaviours (by self)	Establish a method for the person to monitor and record their behaviour(s) as part of a behaviour change strategy	Ask the person to record daily, in a diary, the amount of food they have eaten	Supplementary
	Monitoring of outcome (by self)	Establish a method for the person to monitor and record the outcome(s) of their behaviour as part of a behaviour change strategy	Ask the person to weigh themselves at the end of each day, over a two week period, and record their daily weight on a graph to increase food intake	Supplementary
	Instruction on how to perform behaviour	Advise or agree on how to perform the behaviour (includes ‘Skills training’)	Demonstrate or describe to person how to prepare thickened fluids	Routinely Used
	Information about antecedents	Provide information about antecedents (e.g. social and environmental situations and events, emotions, cognitions) that reliably predict performance of the behaviour	Discuss how people find it difficult to follow their diet when they attend social events	Supplementary
	Prompts/cues	Introduce or define environmental or social stimulus with the purpose of prompting or cueing the behaviour. The prompt or cue would normally occur at the time or place of performance	Put a sticker on fridge to avoid eating cheesecake	Supplementary
	Graded tasks	Set easy-to-perform tasks, making them increasingly difficult, but achievable, until behaviour is performed	Ask patient to consume supplement once per day the first week, then twice per day the second week.	Supplementary
	Body changes	Alter body structure, functioning or support directly to facilitate behaviour change	Prompt use of dentures to promote food consumption	Supplementary

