Review sessions (t_2_-t_18_)^b^	Review goal (behaviour)	Review behaviour goal(s) jointly with the person and consider modifying goal(s) or behaviour change strategy in light of achievement. This may lead to re-setting the same goal, a small change in that goal or setting a new goal instead of (or in addition to) the first, or no change.	Ask if the patient drank the supplement as planned	Routinely Used
	Review goal (outcome)	Review outcome goal(s) jointly with the person and consider modifying goal(s) in light of achievement. This may lead to resetting the same goal, a small change in that goal or setting a new goal instead of, or in addition to the first	Ask if the patient achieved the weight gain goal	Supplementary
	Highlight discrepancy between current and goal (behaviour or outcome)	Draw attention to discrepancies between a person’s current behaviour (in terms of the form, frequency, duration, or intensity of that behaviour) or outcome and the person’s previously set behavioural goals or action plans	Point out that the recorded supplement intake fell short of the goal set	Routinely used
	Monitoring of behaviours (by others, without feedback)	Observe or record behaviour with the person’s knowledge as part of a behaviour change strategy	Have partner observe food intake behaviours and make notes on content and frequency	Supplementary
	Monitoring of behaviours (by others, with feedback)	Monitor and provide informative or evaluative feedback on performance of the behaviour *(*e.g. *form, frequency, duration, intensity)*	Have partner observe food intake behaviours and make notes on content and frequency, inform patient of how many calories they are likely to have ingested per day	Supplementary
	Monitoring of outcome (by others, without feedback)	Observe or record outcomes of behaviour with the person’s knowledge as part of a behaviour change strategy	Weigh the person every two weeks	Supplementary
	Monitoring of outcome (by others, with feedback)	Observe or record outcomes of behaviour with the person’s knowledge and provide informative or evaluative feedback	Inform the person of how much weight they have gained lost following the implementation of a new supplement program	Supplementary

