	Social support (unspecified)	Advise on, arrange or provide social support (e.g. from friends, relatives, colleagues,’ buddies’ or staff) or non-contingent praise or reward for performance of the behaviour. It includes encouragement and counselling, but only when it is directed at the behaviour	Arrange for a partner to encourage patient to use supplements	Supplementary
	Social support (practical)	Advise on, arrange, or provide practical help (e.g. from friends, relatives, colleagues, ‘buddies’ or staff) for performance of the behaviour	Ask the partner to mix the supplement with strawberries for the patient	Supplementary
	Consider pros and cons	Advise the person to identify and compare reasons for wanting (pros) and not wanting to (cons) change the behaviour	Advise the person to list and compare the advantages and disadvantages of drinking the supplement	Supplementary

t_1_ indicates week one of the intervention, t_2_-t_18_ indicates the subsequent weeks of the intervention

^a^Behaviour change techniques have been classified as routinely used techniques to be used with all participants, and supplementary techniques that can be optionally be used

^b^These behaviour change techniques are either tied to subsequent sessions because they cannot logically take place during the first session (e.g. review goals), or they are considered to be secondary techniques that one would use if the initial techniques in the Table above had failed

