### mHealth group

Participants will be provided with a tablet computer (e.g. iPad) and 6 months wireless connectivity if they do not already have access to this equipment. Access to a tablet computer will enable patients to provide fortnightly (or weekly) reports to their dietitian regarding their weight, nutrition impact symptoms (e.g. diarrhoea, mucositis, and nausea) and oral intake so their dietitian can be informed and develop management options prior to their subsequent review via electronic messages. The focus of these consultations is to implement individually tailored, symptom-directed nutritional behavioural management program. Participant engagement in self-monitoring their weight, nutrition impact symptoms, and oral intake using the tablet computer aims to empower and motivate change in dietary behaviours that may be contributing to poor health outcomes [19]. The iPad tool also enables the patient and their carers access to electronic resources that support the nutrition advice.

Communication will be facilitated by a mobile App called MyPace. MyPace has been designed for dietetic practice that supports patient-practitioner relationships [25, 26]. Initial phone contact will occur at baseline to set up the electronic system and complete an initial nutrition assessment. Automated daily reminders will be sent via MyPace to promote behaviour change and adherence. Weight, nutrition impact symptoms (e.g. diarrhoea, mucositis, and nausea) and oral intake will be monitored electronically, and oral nutritional supplements will be recommended as required.

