### Secondary outcomes

We will use the EORTC-C30 scale as a secondary measure of health related quality of life [32]. We have included this tool along with the EQ-5D-5 L as it is a disease-specific quality of life instrument that includes items within several domains that are specific to an oncology population. This tool contains 30 items which are separated into domain scores for global health status, physical function, role function, emotional function, cognitive function, social function, fatigue, nausea and vomiting, pain, dyspnoea, insomnia, appetite loss, constipation, diarrhoea, and financial difficulties. This scale has been shown to have high construct validity, ability to differentiate populations with and without cancer, convergent validity with other health state questionnaires, and high test-retest reliability [32, 33].

Nutritional status will be measured using the Patient-Generated Subjective Global Assessment (PG-SGA) tool. This tool is widely used and has been shown to have reliable clinometric properties when used in the oncology population [34, 35]. The first section of the PG-SGA focuses on four areas and when able, is completed by the participant: weight and weight history, food intake history, nutrition impact symptoms, and activities of daily living and function. The researcher will also complete the second section which incorporates specific disease and its relation to nutritional requirements, metabolic demands, and a physical examination to determine loss of subcutaneous fat and muscle wasting if face-to-face data collection is possible.

Other secondary outcome measures include survival over the 12 month follow up period and changes in self-reported body weight. Where possible (if face-to-face data collection is possible) we will measure waist circumference and hand grip strength using a hand dynamometer (Jamar Digital Hand Dynamometer, Lafayette, Indiana, USA) to support our data relating to changes in nutritional status. For the same reason, tissue density from CT scans taken as routine care pre and 3 month post treatment will be analyzed at the 3rd lumbar vertebra to determine body composition (skeletal muscle, visceral and subcutaneous fat) using Slice-O-Matic software (v.5.0; Tomovision, Montreal, Quebec, Canada).

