### Database extractions

Extraction from hospital databases will be undertaken in an ongoing basis throughout the trial. Extraction from Medical and Pharmaceutical Benefits Scheme databases, and from the Registry of Births, Deaths and Marriages will be completed at the end of the trial.

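### Self-reported body weight is open to reporting error that differs by arm, and no scale weight is planned even where participants are seen face-to-face

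*Protocol article*

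**What the plan says.** The Secondary outcomes section of the Methods defines the outcome: "Other secondary outcome measures include survival over the 12 month follow up period and changes in self-reported body weight". The caption of Fig. 1 also describes weight as self-reported, so this is an explicit choice and not a detail lost in condensing the protocol. The same section lists waist circumference and hand grip strength as staff measurements when contact is face-to-face. It does not list a scale weight. Body composition from routine CT scans is a further supporting measure.

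Weight also features in the intervention. Table 1 gives these examples of techniques for the active arms:
- goal setting: "Set a weight gain goal (e.g. 0.5 kg over one week) as an outcome of changed eating patterns"
- self-monitoring: "Ask the person to weigh themselves at the end of each day, over a two week period"
- review sessions: "Ask if the patient achieved the weight gain goal"

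All three are classed as supplementary, which the table footnote explains as "supplementary techniques that can be optionally be used". For the mHealth group, weight reporting is part of the arm's description: "Access to a tablet computer will enable patients to provide fortnightly (or weekly) reports to their dietitian regarding their weight". The Control group section says that controls receive no extra nutritional advice from the research team.

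The Data collection section sets one method for everyone: interview by a blinded researcher, or self-completion, at baseline, 3, 6 and 12 months. The Randomisation and blinding section names only researchers as blinded.

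**The concern.** A self-reported weight depends on when the participant last stood on a scale and on what answer they feel is expected. The intervention can act on both. A participant who reports weight every week or fortnight, or who has agreed a gain target with a dietitian, may answer the outcome question differently from one who has done neither.

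A blinded interviewer prevents assessor bias but does not affect what the participant says. The linear mixed model in the analysis section adjusts for baseline weight, age, gender, PG-SGA category and cancer location. It cannot remove an error that arises after randomisation and is tied to the arm.

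Two things are at stake. A reporting difference could be read as an effect on weight, or could mask one. The participant-completed part of the PG-SGA includes weight and weight history, so the same error could enter a second nutritional outcome and look like corroboration. The comparison of mHealth with telephone is also exposed, because routine weight reporting is a stated component of only one of those two arms.

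**Working it through.** **Which arm is exposed to what**

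| Feature | Telephone | mHealth | Control |
|---|---|---|---|
| Weight goal, self-weighing, goal review (Table 1) | optional | optional | not offered by the research team |
| Weekly or fortnightly weight reports (mHealth group) | not stated | stated component | not stated |
| Usual dietetic care (Usual care) | yes | yes | yes |
| Outcome weight (Data collection) | same method | same method | same method |

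The method of collection does not differ by arm. What differs is the participant's exposure to weighing and to weight targets before being asked.

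**Timing.** The intervention lasts 18 weeks and is not extended for time in hospital. Three months is about 13 weeks, inside that period. Six months (about 26 weeks) and 12 months (52 weeks) fall after it. The exposure is therefore current at one of the three follow-ups and past at the other two.

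**Direction.** Two mechanisms pull opposite ways:
- Pressure to report reaching a gain target would raise reported weight in the active arms and favour the intervention.
- A control who is losing weight and gives an out-of-date figure reports too high a weight. That hides control loss and works against the intervention.

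The documents do not show which is larger.

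**Illustrative size.** The protocol states no SD and no power for weight. Its sample size is for QALYs, and it reproduces: 2 × (1.960 + 0.842)² / 0.70² = 32.04, rounded up to 33 per group. Recruitment is 37 per group. I use 37, a simple comparison of two means at two-sided 5%, and no true effect. The SD of weight change (5 to 8 kg) and the difference in reporting error, b (0.5 to 1.5 kg), are assumptions.

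SE = SD × √(2/37)
- SD 5: 5 × 0.2325 = 1.16 kg
- SD 8: 8 × 0.2325 = 1.86 kg

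False-positive rate = 1 − Φ(1.96 − b/SE) + Φ(−1.96 − b/SE)

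| b | SD 5 kg | SD 8 kg |
|---|---|---|
| 0.5 kg | 7.1% | 5.8% |
| 1.0 kg | 13.8% | 8.4% |
| 1.5 kg | 25.2% | 12.7% |

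Fewer reported weights make the test less sensitive to a given bias. At 33 per group, an error of 0.2 SD gives 12.8%, against 13.8% at 37. For scale, the retrospective study cited in the Background reported weight losses of 4.2 and 8.9 kg, a difference of 8.9 − 4.2 = 4.7 kg. An error of 1 kg is 1/4.7, about a fifth of that.

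**The case against.** The strongest reply is that the protocol treats the arms alike: one source, one set of time points, blinded collection. That is right. A reader might infer that weight is measured differently by arm, and the documents do not support this. Differential error is a risk inferred from the design, not something the protocol states.

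A reader might also infer that goals and self-weighing are fixed parts of both active arms, that controls have no comparable prompts, and that the bias must favour the intervention. None of these holds:
- The Table 1 techniques on weight are optional. Only mHealth weight reporting is a stated component.
- All participants receive usual dietetic care. Outpatients are screened with the MST, which is based on weight loss and appetite, and Table 2 puts the usual-care delay at about 12 weeks. Some controls may therefore be in dietetic care by the 3-month assessment.
- The direction is open, since out-of-date control weights could work against the intervention.

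It can also be said that weight is only one of several secondary outcomes and that CT body composition is objective. Both are true, and they limit the importance. CT is a partial check only: it comes from routine scans before and 3 months after treatment, is not tied to the 3-, 6- and 12-month assessments, and does not give body weight.

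What remains is that participants know what they receive, that weight is a topic of contact by design in one arm and optionally in another, and that no scale weight is listed at contacts where other body measurements are taken.

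**Conclusion.** The concern holds in limited form. Self-reported weight is open to reporting error that differs by arm, and neither blinded interviewing nor baseline adjustment removes it. The risk is most plausible at 3 months, may extend to the PG-SGA weight section, and leaves the QALY primary outcome untouched. Its sign and size are unknown. Under the assumed SDs of 5 to 8 kg and reporting differences of 0.5 to 1.5 kg, the false-positive rate would lie between about 6% and 25% instead of 5%. Those figures assume 37 reported weights per group and an unadjusted comparison; they show sensitivity and do not estimate the actual bias. This is a cheap improvement to one secondary outcome, not a threat to the trial's main conclusion.

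**What to change.** 1. Take a scale weight at every face-to-face data collection where waist and grip are already measured.
2. Where records are accessible, use a clinic or hospital weight recorded within a stated window around each time point. The Database extractions section says "Extraction from hospital databases will be undertaken in an ongoing basis throughout the trial", but not that weights are held there, so availability must be checked first.
3. Log the source of every weight: scale at visit, record or self-report.
4. Keep self-report where no measured weight exists.
5. Add a sensitivity analysis of the weight outcome limited to measured weights.

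The cost is a scale reading at contacts already planned, a source field and one extra analysis. The record search costs more and will vary by site, since the Economic outcomes section relies on medical records only where accessible. Measured weights will be incomplete and will come selectively from participants who attend or are admitted. The measured-only analysis is therefore supportive and does not replace the main one. Randomisation, sample size and the primary outcome do not change.

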### Economic outcomes

Direct health care costs will be captured by using participant self-report of hospital admissions, hospital records (where accessible), and Medicare and Pharmaceutical Benefits Scheme database extractions. The Medicare and Pharmaceutical Benefits Scheme databases capture all publicly subsidized health care resources consumed in primary care in Australia. The number of days and reasons for hospital admission and outpatient services will be captured from participant self-report and medical records where accessible. Days spent in hospital will be valued using the National Weighted Activity Unit approach which sets prices paid to health services for inpatient and outpatient services provided in Australia (calculator). We will use 2017 as the base year for these calculations.

Productivity costs will be measured using the Productivity Costs Questionnaire (iMTA PCQ). The intent of this measurement is to determine the indirect costs associated with the participant’s health concerns, also known as productivity costs, and whether these are impacted by the intervention. The iMTA PCQ is not disease specific and has been found to be understandable by most of the general population, comprised predominantly of validated questions from previously available instruments [36]. We will use this tool to assess the capacity of participants to perform paid or unpaid work over the trial period, to facilitate the valuation of productivity losses and ensure that the economic evaluation is complete.

### Database extractions

Extraction from hospital databases will be undertaken in an ongoing basis throughout the trial. Extraction from Medical and Pharmaceutical Benefits Scheme databases, and from the Registry of Births, Deaths and Marriages will be completed at the end of the trial.

### Data analysis

The advisory committee will review data cleaning. A mixed methods approach to analysis will comprise a clinical effectiveness study and a concurrent and cost-utility economic evaluation. The primary outcome will be health-related quality of life, converted to quality-adjusted life years lived. Multiple imputation will be used to replace missing individual data points for conducting comparisons in mean QALYs per participant between groups.

### Sample size calculation

A sample size of *n* = 33 participants per group is estimated to attain 80% power to identify a smaller standardised difference (0.70) for comparisons with the control group at the alpha = 0.05 level on the QALY lived outcome. We will therefore recruit *n* = 37 per group to account for potential drop-outs from this study (note – there were zero drop-outs for reasons other than death, from our pilot study with *n* = 21).

